**Ethical consideration**

This protocol will be submited to the collage of Public Health and Medical Sciences of ethical committee of Assasa University for approval and obtain ethical clearance letter from the committee before data collection start. A written letter of permission from BGRS Health Bureau and Drug Administration and Control Agency (DACA) will be obtained prior data collection. Written and oral consent of each respondent will also obtain to participate on the study after explaining the aim of the study.

**Limitation and strength of the study**

**Limitation of the study**

Even though it is seasonal, Bullen district is one of the malarious areas in Ethiopia, which has high malaria transmission rate, and so within the follow up of 28 days of WHO protocol, there may be a possibility of re-infection, which cannot be identified without the help of molecular technique (PCR).

**Strength of the study**

The study will use WHO protocol for the efficacy test of CQ. In addition, it provides information on the drug effectiveness status of the town and gives strength for interpretation of the drug response in combination with other parameters.

**Operational definitions and study end points/outcomes**

**Early treatment failure (ETF):** includes any of the following:

• Development of danger signs or severe malaria on Day 1, Day 2 or Day 3, in the presence of parasitaemia

• Parasitaemia on Day 2 higher than Day 0 count irrespective of axillary temperature

• Parasitaemia on Day 3 with axillary temperature ≥37.5 °C

• Parasitaemia on Day 3 ≥ 25% of count on Day 0.

**Late Clinical Failure (LCF)**

• Development of danger signs or severe malaria after Day 3 in the presence of parasitaemia, without previously meeting any of the criteria of *Early Treatment Failure*

• Presence of parasitaemia and axillary temperature ≥37.5 °C (or history of fever) on any day from Day 4 to Day 28, without previously meeting any of the criteria of *Early Treatment Failure*

**Late Parasitological Failure(LPF)**

• Presence of parasitaemia on any day from Day 7 to Day 28 and axillary temperature < 37.5 °C, without previously meeting any of the criteria of *Early Treatment Failure* or

*Late Clinical Failure*

**Adequate Clinical and Parasitological Response(ACPR)**

Absence of parasitaemia on Day 28 irrespective of axillary temperature without previously meeting any of the criteria of Early Treatment Failureor Late Clinical or Failure or Late Parasitological Failure is taking as ACPR.

**Time to fever clearance (FCT)**: Time to fever clearance is define as time from first dose until the first time the body temperature decreased below and remained below 37.5° C for at least a further 48 hours.

**Safety and tolerability -** The incidence of any adverse event will be documented. All patients will be asked routinely about previous symptoms and about symptoms that have emerged since the previous follow-up visit. When clinically indicated, patients will be evaluated and treated appropriately.

**Parasite clearance time**- defined as the first thick film negative for two consecutive days and

**Fever clearance time** - axillary temperature below 37.50C for two consecutive days

**Sever malaria:** Severe manifestation of malaria in adults and children will be considered through Clinical manifestations and Laboratory findings.When a patient manifest Prostration, impaired consciousness, respiratory distress, multiple convulsions, circulatory collapse, pulmonary edema, abnormal bleeding, jaundice and haemoglobinurea clinically moreover, laboratory results helps to confirm the disease severity. Findings which help for classification of Severe malaria includes sever anaemia having haemoglobin level of < 5 g/dl or haematocrit < 15%. In addition, hypoglycemia with blood glucose level < 2.2 mmol/l or 40 mg/dl, acidosis (plasma bicarbonate < 15 mmol/l), hyperlactataemia (venous lactic acid > 5 mmol/l), hyperparasitaemia (>4% in non-immune patients), renal impairment (serum creatinine above normal range for age) and among childrenthe occurrence oftwo or more convulsions within 24 h and persistent vomiting will be considered as sever malaria infection.

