**Measurements**

**Variables**

**Dependant variables**

- A 28 days of CQ efficacy/clinical and parasitological outcome after treatment through the following methods:
- **Hemoglobin concentration:** Hemoglobin will be determined through Hem cue heamatological analyzer or through haematocrit at days of 0, and 28 of time schedule to check the improvement of the patients’ heamoglobine level, which indicates indirect evaluation of the drug efficacy.
- **Clinical signs and symptom consideration:** the clinical outcome of patients after treatment will be assessed and recorded according to the protocol of WHO (2009).
- **Parasitic loads:** Parasitic load will be quantitate according to the schedule of WHO protocol (day 0, 1, 2, 3, 7, 14, 21and 28 day), and will help for the classification of the drug response.
- Early Treatment Failure (ETF)
- Late Clinical Failure (LCF)
- Late Parasitogical Failure (LPF)
- Adequate Clinical and Parasitological Response (ACPR)
- **Time to fever clearance (FCT)**: Time to fever clearance will be record according to the WHO protocol.
- **Safety and tolerability**: The incidence of any adverse event will be documented. All patients will be asked routinely about previous symptoms and about symptoms that have emerged since the previous follow-up visit through checklists. When clinically indicated, patients will be evaluated and treated appropriately. All adverse events will be recorded on the case report form.

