**Quality control**

Clinical examination and parasite counts will be perform every day for two consecutive days whether the parasites and symptoms are completely cleared or not and continuous check up will be perform weekly from day 7 of the first drug administration till 28 days of total follow up days. Axillary temperatures will record every day of the first two days during blood sample collection. Primary end points of the study are the parasitological and clinical response to treatment. All slides on day 0, all positive slides after day 7 (regardless of the parasite species) and 10% randomly selected negative slides will crosschecked by a senior laboratory technician who are engaged in the regional laboratory. The machine that can measure heamoglobin will be calibrated and adjust through standards and, reagents like Giemsa stains will be check by the known positive samples. In addition, for the laboratory technicians, if necessary refreshment course on the identification and enumeration of the parasites will be provide.

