**Microscopic blood examination**

Thick and thin blood films for parasite counts will be obtained and exam­ined at screening on day 0 to confirm adherence to the inclusion and exclu­sion criteria. Thick blood films will be also examined on days 2, 3, 7, 14, 21and 28, or any other day if the patient returns spontaneously and parasitological reassessment is required. Specimens will be labelled anony­mously (screening number or study number, day of follow-up, date).

A fresh Giemsa stain dilution (10%v/v) will be prepared at least once a day and possibly more often, depending on the number of slides to be processed. Giemsa-stained thick and thin blood films will be examined at a magnifica­tion of 1000× to identify the parasite species and to determine the parasite density.

Two blood slides per patient will be obtained: one thick blood smear and one thin blood smear. Thick blood slide will be stained by 10% Giemsa for 10–15 min for initial screening. Moreover, if the patients are subsequently enrolled, the same staining will be used for all slides obtained at follow-up visits. The study number of the patient, the date and the day of follow-up will be recorded either on the frosted edge of the slide or on the glass with a permanent glass pen.

The thick blood smear for initial screening will be used to count the numbers of asexual parasites and white blood cells in a limited number of microscopic fields.

Thin blood smear will be used to calculate the parasite density, by counting the number of asexual parasites in a set number of white blood cells (typically 200), using the following formula:

Parasite density (per µl) =
[figure not shown]

[figure not shown]

The same technique will be used to establish the parasite count on each subsequent blood film. When the number of asexual parasites is less than 10 per 200 white blood cells in follow-up smears, counting will be done against at least 500 white blood cells (i.e. to completion of the field in which the 500th white blood cell is counted). A blood slide will be considered negative when examination of 1000 white blood cells reveals no asexual parasites. The presence of gametocytes on an enrolment or follow-up slide will be noted, but this information will not contribute to basic evaluation.

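### Fever clearance has two conflicting definitions, and under the two-consecutive-day rules a first clearance on Day 3 or later cannot be confirmed at the routine visits, whose days also differ between sections

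*Protocol*

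**What the plan says.** All three clearance definitions stand in the protocol's operational definitions, after the paragraph on adequate clinical and parasitological response.

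- Fever clearance, first definition: "time from first dose until the first time the body temperature decreased below and remained below" 37.5 °C "for at least a further 48 hours". The origin is the first dose and the site of measurement is not given.
- Fever clearance, second definition: "axillary temperature below 37.50C for two consecutive days" (the printed figure is 37.5 °C). The site is axillary and no time origin is given.
- Parasite clearance: "defined as the first thick film negative for two consecutive days and".

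Time to fever clearance is listed among the dependent variables. Parasite clearance time is defined but not listed there. The abstract says that changes in both will be evaluated at each follow-up visit.

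The days of measurement appear in several places:

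- The abstract evaluates clinical and parasitological outcomes on Days 1, 2, 3, 7, 14, 21 and 28.
- Under Dependant variables, parasite load is measured on "day 0, 1, 2, 3, 7, 14, 21and 28 day".
- Under Microscopic blood examination: "Thick blood films will be also examined on days 2, 3, 7, 14, 21and 28", after a Day 0 film. There is no routine Day 1 film.
- Under Quality control, "parasite counts will be perform every day for two consecutive days", with weekly checks from Day 7. Axillary temperature is recorded on the first two days.
- The definition of early treatment failure needs an axillary temperature on Day 3.

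**The concern.** One planned outcome has two definitions, and nothing says which governs. They differ in the length of time below threshold, the site of measurement and the time origin, so the same temperature chart can give two answers.

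Separately, a rule that asks for two consecutive days needs two visits one day apart. Such visits exist only in the first three days. A patient who clears later cannot meet the rule at the routine visits, however well the patient does afterwards. If clearance times are then summarised among patients who have a value, the slower clearers drop out and the summary looks faster than the truth.

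The conflicting schedules add to this, because the set of patients who can have a value depends on which section the site follows.

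**Working it through.** No sample-size or power formula applies, and the protocol gives no figure to reproduce. The check is an enumeration of definitions against visit days.

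**Step 1: two-consecutive-day rule.** A first clearance on Day d can be confirmed only if Days d and d+1 are both post-dose visit days. From Day 7 on, all schedules are weekly, so no later pair exists.

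| Source | Routine post-dose days to Day 7 | Consecutive pairs | First clearance that can be confirmed |
|---|---|---|---|
| Abstract; Dependant variables | 1, 2, 3, 7 | (1,2), (2,3) | Day 1 or 2 |
| Microscopic blood examination (films) | 2, 3, 7 | (2,3) | Day 2 only |
| Quality control, if its two days are Days 1 and 2 | 1, 2, 7 | (1,2) | Day 1 only |
| Quality control, if its two days are Days 0 and 1 | 1, 7 | none | none |

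A first negative film on Day 3 has its next routine film on Day 7, 7 − 3 = 4 days later, so it never meets the rule. With the annex film days, clearance on Day 1 cannot be told from clearance on Day 2. The two-day fever rule gives the values in the first row if temperature is taken at each visit.

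**Step 2: 48-hour rule.** Take temperatures on Days 1, 2, 3 and 7.

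- Low from Day 1: Day 1 to Day 3 is 2 × 24 = 48 hours, so it can be confirmed by Day 3.
- Low from Day 2: Day 2 to Day 3 is 24 hours. The next reading is Day 7, 5 × 24 = 120 hours after Day 2.
- Low from Day 3: the next reading is Day 7, 4 × 24 = 96 hours later.

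Under the temperature sentence in Quality control, two daily readings span 24 hours, so the 48-hour rule cannot be confirmed for anyone. That sentence also conflicts with the Day 3 temperature that early treatment failure requires.

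**Step 3: do the two fever rules agree?** Write A for afebrile and F for febrile on Days 1, 2 and 3, giving 2³ = 8 patterns, judged on those three readings.

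| Pattern | 48-hour rule | Two-day rule |
|---|---|---|
| AAA | Day 1 | Day 1 |
| AAF | not cleared on Day 1 | Day 1 |
| FAA | not confirmed by Day 3 | Day 2 |
| FFF, FFA, FAF, AFF, AFA | no value by Day 3 | no value |

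They part in 2 of 8 patterns, AAF and FAA.

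**Step 4: let the Day 7 reading confirm the 48-hour rule.** Suppose Day 7 is afebrile. FAA is then Day 2 under both rules, so that disagreement goes. AAF still differs. FFA and AFA now get Day 3 under the 48-hour rule and no value under the two-day rule. The conflict moves but does not vanish.

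**The case against.** A reader might infer that neither clearance time can be measured at all. The documents do not support that. With visits on Days 1, 2, 3 and 7, parasite clearance and the two-day fever rule can be resolved to the day for first clearance on Day 1 or 2.

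A reader might also infer that every patient with a parasite clearance value gets Day 2. That follows only from the annex film days. The abstract and the list of dependent variables include Day 1, and the annex allows extra films when a patient returns spontaneously, which could create further pairs.

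The 48-hour definition does not demand daily readings. A patient below threshold on Days 3 and 7 was below at every scheduled reading over more than 48 hours, so it is reasonable to accept the next visit as confirmation. This stands. It means that the absence of a value for Day 3 clearers is firm for the two-consecutive-day rules, but not for the 48-hour rule when temperature is taken on Day 7.

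On importance, the introduction's remark that clearance times give early warning of resistance is general background, not a stated use in this study. Day 3 parasitaemia with fever, or at 25% or more of the Day 0 count, already counts as early treatment failure, so slow response is not wholly lost. This also stands and limits the weight of the point.

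Finally, interval censoring is detail that an analysis plan may supply. It may, but it would still inherit two fever definitions and three versions of the schedule from the protocol.

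**Conclusion.** The point holds for secondary outcomes. The protocol gives two incompatible definitions of fever clearance, which part in 2 of 8 Day 1 to 3 patterns; accepting Day 7 as confirmation changes which patterns differ but does not remove the conflict. The two-consecutive-day rules can be confirmed only for first clearance on Day 1 or 2, or Day 2 alone with the annex's routine films. Patients who first clear on Day 3 or later have no valid value under those rules, so a summary among patients with a value leans towards fast clearance. The schedules in the abstract and list of dependent variables, the microscopy annex and Quality control disagree with one another, and Quality control's temperature days disagree with the definition of early treatment failure.

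This rests on routine visits only and on one reading per visit. The size of the lean cannot be given, because the protocol has no expected distribution of clearance times. The 28-day failure risk by Kaplan-Meier does not use these definitions and is unaffected.

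**What to change.** 1. Keep one definition of fever clearance, with its site of measurement and time origin, and delete the other.
2. Reconcile the film and temperature days in the abstract, Dependant variables, Quality control, Microscopic blood examination and the definition of early treatment failure, so that they state one schedule.
3. Report the proportion with axillary temperature below 37.5 °C and the proportion film-negative at each scheduled visit (Days 1, 2, 3 and 7, if those are the days kept). If a time is wanted, treat it as interval-censored between the last positive and the first negative visit, confirmed at the next scheduled visit. Slower clearers then stay in the summary.
4. Base fever clearance on patients with fever at Day 0. The annex's inclusion criteria admit patients on a history of fever alone, and for them a time to clearance has no clear meaning. The main inclusion list names a measured temperature without that alternative, so the two lists should be read together when this is written.

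The cost is wording and a simpler table. The changes to definition and reporting need no extra visits. The downside is a coarser outcome than a time in hours.

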**Uncomplicated malaria:**

**Resistance**: the ability of a parasite strain to survive and/ or multiply despite the administration and absorption of a drug given in doses equal to or higher than those usually recommended but within the tolerance of the subject.”

**Dissemination of the result**

The final reportwill be disseminate to the collage of public health and medical sciences of Assosa University, BGRS health bureau and an effort will be made to present to the scientific community through publications and presentation; to the broader community through magazine and other channels in and outside.

**Work plan(2014)**

| Tasks to be Performed | Responsible Person | periods | | | | | | | | | | | |
| --- | --- | --- | --- | --- | --- | --- | --- | --- | --- | --- | --- | --- | --- |
| May | Jun. | Jul. | Aug. | Sep. | Oct. | Nov. | Dec. | Jan. | Feb. | Mar. | Apr. |
| Topic selection | PI |  |  |  |  |  |  |  |  |  |  |  |  |
| Approval & Finalize research proposal | PI |  |  |  |  |  |  |  |  |  |  |  |  |
| Submission of it to ethical clearance committee | PI |  |  |  |  |  |  |  |  |  |  |  |  |
| Collection of budget, material and other resources | PI |  |  |  |  |  |  |  |  |  |  |  |  |
| Written consent from respective bodies | PI |  |  |  |  |  |  |  |  |  |  |  |  |
| Training data collectors | PI |  |  |  |  |  |  |  |  |  |  |  |  |
| Data collection and organization | PI |  |  |  |  |  |  |  |  |  |  |  |  |
| Data analysis & interpretation and draft write up | PI |  |  |  |  |  |  |  |  |  |  |  |  |
| Final report dissemination | PI |  |  |  |  |  |  |  |  |  |  |  |  |
| Monitoring and evaluation | PI |  |  |  |  |  |  |  |  |  |  |  |  |

# Budget break down

Chemicals and reagents

| Serial no | Items | Unit | Quantity | Unit Price | | Total Price | | |
| --- | --- | --- | --- | --- | --- | --- | --- | --- |
| Birr | Cents | Birr | | Cents |
|  | Microscopic slide | Pack | 20 | 49 | 00 | 980 | 00 | |
|  | RDT | Kits | 550 | 15 | 00 | 8250 | 00 | |
|  | Cotton | pack | 5 | 14 | 75 | 82 | 35 | |
|  | 70% Alcohol | Liter | 5 | 18 | 20 | 91 | 00 | |
|  | Syringes | Pack | 450 | 10 | 00 | 4500 | 00 | |
|  | EDTA Test tube | Pack | 100 | 25 | 00 | 2500 | 00 | |
|  | Lancet | Pack | 3 | 40 | 35 | 121 | 15 | |
|  | Giemsa stains | Liter | 15 | 20 | 00 | 300 | 00 | |
|  | Methyl alcohol | Liter | 2 | 90 | 85 | 181 | 70 | |
|  | Distilled water | Liter | 20 | 10 | 25 | 205 | 00 | |
|  | Oil immersion | Bottle | 3 | 10 | 45 | 31 | 15 | |
|  | 5% Bleach | Liter | 5 | 100 | 00 | 500 | 00 | |
|  | Washing soap | Pcs | 10 | 10 | 00 | 100 | 00 | |
|  | Slide box | Pieces | 4 | 45 | 75 | 182 | 15 | |
|  | Digital camera | Pieces | 1 | 2000 | 00 | 2000 | 00 | |
|  | Examination Glove | Pack | 5 | 30 | 00 | 150 | 00 | |
|  | Heavy duty glove | Pcs | 5 | 20 | 00 | 100 | 00 | |
|  | Capillary tubes | Pack | 5 | 100 | 00 | 500 | 00 | |
|  | Sealant | Pack | 3 | 50 | 00 | 150 | 00 | |
| **Sub total** | | | | | | **20, 923** | **00** | |

**Stationary materials**

| S.No. | Items  Materials | Unit | Quantity | Unit price | | Total price | |
| --- | --- | --- | --- | --- | --- | --- | --- |
| Birr | Cent | Birr | Cent |
|  | Typing paper | Pieces | 3 | 80 | 00 | 240 | 00 |
|  | Duplicating paper | Pieces | 20 | 75 | 00 | 1500 | 00 |
|  | Pen | Pcs | 7 | 2 | 00 | 14 | 00 |
|  | Pencil | Pcs | 15 | 0 | 50 | 7 | 50 |
|  | Binder | Pieces | 10 | 5 | 00 | 50 | 00 |
|  | Flash disc | Pieces | 1 | 250 | 00 | 250 | 00 |
|  | CD | Pieces | 5 | 10 | 00 | 50 | 00 |
|  | Fuel | Litter | 50 | 12 | 00 | 600 | 00 |
|  | Marker | Pcs | 10 | 20 | 00 | 200 | 00 |
| Total | | | | | | **2911** | **00** |

Man power

| No | Man power | Quantity | Fee/day | Total working days | Total fee in birr |
| --- | --- | --- | --- | --- | --- |
|  | Physician | 1 | 140 | 25 | 3500 |
|  | Data collector (Nurses) | 2 | 70 | 25 | 3500 |
|  | Laboratory Technologists | 4 | 70 | 25 | 7000 |
|  | Driver | 1 | 58 | 20 | 1160 |
|  | Supervisor | 1 | 70 | 20 | 1400 |
|  | Technical staff | 1 | 70 | 15 | 1050 |
|  | Secretary | 1 | 47 | 10 | 470.00 |
| Sub Total | | | | | **18, 080** |

Grand total = 20923+2911+18080 = **41914**

10 % contingency from materials = **4191.4** birr

Therefore, net budget = **41914+4191.4** = **46,105.40 birr**

**Annex-1 Laboratory procedures**

**3.1.** Method of sample collection capillary blood collection

1. Rub the site vigorously with cotton or a gauze pad moistened with 70% alcohol
2. After the skin has dried, make a puncture 2-3mm deep with a sterile lancet. A rapid and firm puncture should be made with control of the depth
3. a freely flowing blood should be taken and will make thick and thin blood films.
4. Stop the blood flow by applying slight pressure at the site preferably with a gauze pad

Preparation of thick blood film

- Place a small drop of blood on a clean slide
- spread it with an applicator stick or the corner of another slide until small prints are just visible through the blood smear
- The prepared smear corresponds to a circle of approximately 2cm diameter.

Preparation Thin blood film

1. Place a small drop of well mixed EDTA blood (about 2-3 mm) or freshly collected from capillary blood sites , 1.0 cm from the end of the glass slide, using either a plain capillary tube or other type of blood dropping device

- when the blood is from an anemic patient larger drop of blood should be used
- If capillary blood to be used, the procedure will follow SOP for proper collection of capillary blood

1. the spreading slide is placed in front of the drop of blood at an angle of about 30o - 40 o to the slide and then is moved back to make contact with the drop (both the spreader and the base slide should be free from grease)
2. The drop will spread out quickly along the line of contact of the spreader with the slide
3. As the drop of blood spreads, be careful not to let it spread to both edges of the spreader
4. The spreader is advanced with a smooth steady motion so that a thin film of blood is spread over the slide
5. Allow the smear to air-dry

- Also do not use heat for drying

1. Label the name of the patient and date or reference number is written on the head of the film using a lead pencil, a diamond marker or a graphite

